## 5.2 Contraception Recommendations

---

### Contraception Requirements for Females

Subjects must follow the following contraceptive guidelines as specified:

- Females, Non-Childbearing Potential

Females do not need to use birth control during or following study drug treatment if considered of non-childbearing potential due to meeting any of the following criteria:

- Postmenopausal, age > 55 years with no menses for 12 or more months without an alternative medical cause.
- Postmenopausal, age ≤ 55 years with no menses for 12 or more months without an alternative medical cause and a follicle-stimulating hormone level > 40 IU/L.
- Permanently surgically sterile (bilateral oophorectomy, bilateral salpingectomy, or hysterectomy).

- Females, of Childbearing Potential

Females of childbearing potential must avoid pregnancy while taking study drug(s) and for at least 185 days after the last dose of study drug. Females must commit to 1 of the following methods of birth control:

- Combined (estrogen and progestogen containing) hormonal birth control (oral, intravaginal, transdermal, injectable) associated with inhibition of ovulation initiated at least 30 days prior to study Baseline Day 1, in combination with a barrier method(s) as drug-drug interactions with ABBV-467 with the hormonal contraception are unknown.
- Progestogen-only hormonal birth control (oral, injectable, implantable) associated with inhibition of ovulation initiated at least 30 days prior to study Baseline Day 1, in combination with a barrier method(s) as drug-drug interactions with ABBV-467 with the hormonal contraception are unknown.
- Bilateral tubal occlusion/ligation (can be via hysteroscopy, provided a hysterosalpingogram confirms success of the procedure).
- Intrauterine device (IUD).
- Intrauterine hormone-releasing system (IUS).
- Vasectomized partner (provided the partner has received medical confirmation of the surgical success of the vasectomy and is the sole sexual partner of the trial subject).
- Practice true abstinence, defined as: Refraining from heterosexual intercourse when this is in line with the preferred and usual lifestyle of the subject (periodic abstinence [e.g., calendar, ovulation, symptothermal, post-ovulation methods] and withdrawal are not acceptable).
- If required per local practices, male or female condom with or without spermicide or cap, diaphragm or sponge with spermicide should be used in addition to 1 of the birth control methods listed above (excluding true abstinence).

Contraception recommendations related to use of concomitant therapies prescribed should be based on the local label.

### Contraception Requirements for Males

Male subjects who are sexually active with a female partner of childbearing potential, must agree **to use condoms, even if the male subject has undergone a successful vasectomy**, from C1D1 through at least 95 days after the last dose of study drug:

- His female partner(s) must also use at least 1 of the following methods of birth control:
  - Combined (estrogen and progestogen containing) hormonal birth control (oral, intravaginal, transdermal, injectable) associated with inhibition of ovulation initiated at least 30 days prior to study Baseline Day 1.
  - Progestogen-only hormonal birth control (oral, injectable, implantable) associated with inhibition of ovulation initiated at least 1 month prior to study Baseline Day 1.
  - Bilateral tubal occlusion/ligation (can be via hysteroscopy, provided a hysterosalpingogram confirms success of the procedure).
  - IUD.
  - IUS.

## 5.3 Prohibited Medications and Therapy

---

No anticancer agents, radiation, anticancer medicinal/herbal remedies, investigational agents, anticancer corticosteroid therapy, or anticancer hormonal therapy may be taken while the subject is in the treatment phase of the study. However, during the dose escalation part of the study only, localized radiation therapy to a site of pre-existing and/or symptomatic disease may be permitted. Following approval from the sponsor, a subject may initiate or continue with protocol therapy without interruption during the course of palliative radiation therapy if the investigator believes that the risk of excessive bone marrow suppression or other toxicity is acceptable, and it is in the best interest of the subject.

Extramedullary sites of MM or AML identified at baseline that are surgically resected or in any radiated fields should be excluded from further response assessments.

Use of radiotherapy or surgical intervention must be recorded on the electronic case report form (eCRF).

Medications known to prolong the QT interval (Operations Manual Section 7.6) are prohibited.

## 5.4 Prior and Concomitant Therapy

---

Any medication or vaccine (including over the counter or prescription medicines, vitamins, and/or other supplements) that the subject is receiving at the time of enrollment or receives during the study must be recorded through the follow-up visit.

Best supportive care and treatment in accordance with standard practice (antiemetics, antibiotics, transfusions, oxygen therapy, nutritional support, palliative treatment for pain or cough, etc.) will be given as appropriate to each subject. Any questions regarding concomitant or prior therapy should be raised to the AbbVie emergency contact. Information regarding potential drug interactions with ABBV-467 can be located in the ABBV-467 Investigator's Brochure.

Medications that may be required during the first 15 days of Cycle 1 to reduce the risk of tumor lysis syndrome (TLS) include the following:

- Allopurinol or other appropriate TLS risk-reducing agent required through Day 15 of Cycle 1.
- Adequate fluids to ensure dehydration prevention (note: per institutional standards while using medical judgment; refer to [Appendix G](#)).

In addition, use of hydroxyurea is recommended as needed to maintain a white blood cell count of < 25,000/ $\mu$ L during Cycle 1 of the study.

MM subjects only: In dose escalation, hematopoietic growth factors and transfusion support should not be given during the DLT evaluation period, but are otherwise permitted at the investigator's discretion, in accordance with local or institutional guidelines and/or practice patterns.

The following medications are to be used with caution during the study (see Operations Manual Section 7.5 for examples of each):

- P-glycoprotein inhibitors.
- Breast cancer resistance protein inhibitors.
- OATP1B1/B3 inhibitors.
- OATP1B1/1B3 substrates.
- Strong CYP3A4 inhibitors.

Subjects who are receiving corticosteroids chronically (> 3 months) for non-oncological purposes may continue at a dose that does not exceed 5 mg per day of prednisone or equivalent.

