## Tumor Lysis Syndrome

Subjects with MM with high tumor burden (e.g., high bone marrow plasma cell infiltration, plasma cell leukemia, or bulky plasmacytomas), rapidly increasing M-protein or light chains or high proliferative activity, plasmablastic morphology, or compromised renal function ( $CrCl < 50$  mL/minute) may be at higher risk of developing TLS. There is a potential risk for TLS in subjects with AML, especially in those with elevated leukocyte count, circulating blasts, elevated pretreatment lactate dehydrogenase levels, renal dysfunction, and dehydration. To mitigate the risk for TLS all subjects enrolled into the study will need TLS prophylaxis and monitoring. For subjects at higher risk for TLS, additional mitigation measures with more intensive laboratory monitoring and intervention should be implemented. Prophylactic reductions of potassium, inorganic phosphorus or uric acid above normal range are recommended prior to beginning study treatment and to be continued based on the ongoing risk of TLS. Please reference [Appendix F](#) for additional information on the evidence of TLS and [Appendix G](#) for initial management of electrolyte abnormalities and prevention of TLS.

During dose escalation, each subject should be hospitalized the night prior to C1D1 for hydration, treatment with uric acid-reducing agents, and monitoring. Tumor lysis syndrome laboratories will be obtained at 3 different time points: immediately prior to the first dose, 6 to 8 hours after the first dose, and approximately 24 hours after the first dose (on C1D2).

The subject may be discharged once the laboratory results on C1D2 are reviewed (approximately 24 hours after first dose) and confirm the absence of TLS. If discharged since first dose, subjects will be re-hospitalized the night prior to C1D8 for hydration, treatment with uric acid-reducing agents, and monitoring.

Tumor lysis syndrome prophylaxis and management for the second dose of ABBV-467 will be managed in the same manner as the first dose described above. Subjects who experience clinical or laboratory TLS, or other significant toxicity following the first or second dose of ABBV-467 should discuss the safety monitoring plan for subsequent doses of ABBV-467 with the AbbVie TA MD.

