The Sponsor will review the totality of clinical and laboratory data on an ongoing basis and may provide additional recommendations regarding the need for subject monitoring, including either removing the need for, or extending required duration of, any hospitalization.

**Below are the minimum requirements for TLS prophylaxis and management for all subjects enrolled into the study.** All other prophylaxis and monitoring procedures for TLS will be implemented as per regional guidelines/institutional standards:

- All subjects must receive uric acid reducing agent, adequate oral and IV hydration as tolerated while monitoring the fluid status of the subject prior to and during the first cycle of treatment. The uric acid reducing agent, type of fluids and the rate of infusion will be determined by the investigator based on regional standards or institutional guidelines.
- TLS chemistry tests to be drawn (calcium, inorganic phosphorus, potassium, uric acid, and creatinine) on the first day of dosing and each day of a new dose at 0 (within 4 hours prior to dosing) and 6 – 8 hours post dose.
- Additional laboratory assessments may be performed, per investigator discretion, post-dose and up to 48 hours, if clinically indicated.

Abnormal chemistry tests should be corrected promptly. If a subject meets criteria for clinically significant laboratory or clinical TLS ([Appendix F](#)), institutional guidelines or recommendations in [Appendix G](#) should be followed, no additional doses should be administered until resolution. For continued dosing, monitor for evidence of TLS during study treatment, and manage abnormalities of serum creatinine, and electrolytes promptly.

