| Vital Signs                            | ✓                                | ✓              | ✓                   | ✓                                    |                          | ✓                                | ✓                                         | ✓           | ✓                              |                                                          |
| ECOG Performance Status                | ✓                                | ✓              |                     |                                      |                          | ✓                                |                                           | ✓           | ✓                              |                                                          |
| Targeted Physical Examination          | ✓                                | ✓              |                     |                                      |                          | ✓                                |                                           | ✓           | ✓                              |                                                          |
| Height (screening only) and Weight     | ✓                                | ✓              |                     |                                      |                          | ✓                                |                                           | ✓           | ✓                              |                                                          |
| TLS Prophylaxis                        |                                  | ✓              | ✓                   | ✓                                    |                          |                                  |                                           |             |                                |                                                          |
| TLS Chemistry Panel                    |                                  | ✓              | ✓
D2
only     | ✓                                    |                          |                                  |                                           |             |                                |                                                          |

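### Section 5.4 ends the required tumor lysis agent at Day 15 of Cycle 1, while the Section 6.2 minimum and both visit schedules extend prophylaxis to the Day 22 dose

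*Protocol*

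**What the plan says.** Section 5.4 (Prior and Concomitant Therapy) introduces a short list with "Medications that may be required during the first 15 days of Cycle 1 to reduce the risk of tumor lysis syndrome (TLS". The list holds two items, the agent and adequate fluids. For the agent it says "Allopurinol or other appropriate TLS risk-reducing agent required through Day 15 of Cycle 1". The limit to the first 15 days thus appears twice, once over the whole list and once on the agent.

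Section 6.2 (Tumor Lysis Syndrome) opens its list with "Below are the minimum requirements for TLS prophylaxis and management for all subjects enrolled into the study". The first item reads "All subjects must receive uric acid reducing agent, adequate oral and IV hydration as tolerated", and after a clause on monitoring fluid status it gives the period as "prior to and during the first cycle of treatment". Section 4.1 defines Cycle 1 as 28 days.

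Appendix D has a row headed "TLS Prophylaxis", ticked for Cycle 1 Day 1, for Days 2 to 5, and in the shared column for Days 8, 15 and 22. The last tick has no day restriction. Operations Manual Section 2.1 also lists TLS prophylaxis for the Cycle 1 Day 8, 15 and 22 visits without restriction.

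**The concern.** Four places in one document state when TLS prophylaxis applies in Cycle 1. Three of them reach the Day 22 infusion, and Section 5.4 stops a week earlier. Section 5.4 is the concomitant therapy section, and Operations Manual Section 3.3 refers readers to Sections 5.3 and 5.4 for general guidance on prohibited, cautionary and allowed medication. A site could reasonably write its orders from there.

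The dose at stake is a full-target-dose infusion in a first-in-human study, inside the 28-day DLT window. A site that followed Section 5.4 literally would omit an agent that Section 6.2 makes mandatory and would contradict its own visit checklist. Section 5.9 bars deviations except to remove an immediate hazard and requires that they be notified, so following Section 5.4 could also create reportable deviations.

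**Working it through.** The plan gives no figure on this point to reproduce. The check is a comparison of the texts and a count of days.

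**The four statements side by side**

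| Place | Status | Period |
|---|---|---|
| Section 5.4 | Lead-in is conditional; bullet is mandatory | To Day 15 of Cycle 1 |
| Section 6.2 | Stated minimum for all subjects | Before and during Cycle 1 (28 days) |
| Appendix D | Scheduled activity | Days 1, 2–5, 8, 15, 22 |
| Operations Manual 2.1 | Scheduled activity | Days 8, 15, 22 (Days 1 and 2–5 are listed separately) |

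**Is the Day 22 entry deliberate?** In the same Appendix D column, triplicate ECG and troponin are restricted to Day 15 and hospitalization to Day 8. The Operations Manual list carries the same restrictions. The schedules mark a day limit where one is meant, and TLS prophylaxis has none.

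**Day and dose counts**

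- Cycle 1 infusions fall on Days 1, 8, 15 and 22, so there are 4. Under Section 4.1 Day 1 is at half dose and the other 3 are at full target dose. Day 22 is 1 of 4 and the third at full dose.
- Shortfall to the Day 22 dose: 22 − 15 = 7 days (Days 16 to 22).
- Shortfall to the end of Cycle 1: 28 − 15 = 13 days (Days 16 to 28).

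**Counts that bear on the likely clinical effect**

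- TLS panels in Operations Manual Table 8: 3 (Day 1) + 3 (Day 8) + 1 (Day 15) + 1 (Day 22) = 8. The first two doses account for 6, and 6/8 = 75%. Table 8 gives Day 22 a pre-infusion panel only.
- Appendix F confines laboratory TLS to a window ending 7 days after the start of therapy. Day 22 is 22 − 1 = 21 days after the first dose, which is 21 − 7 = 14 days beyond that window if it runs from the first dose.

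These are counts of days, infusions and panels. None of them estimates TLS risk.

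**The case against.** The strongest reply is that the protocol already shows which text governs. Section 6.2 calls its list a minimum, and Section 5.4 sets no maximum and does not tell sites to stop the agent. A site that follows Section 6.2 through Cycle 1 also satisfies Section 5.4. The TLS-specific pointers in Operations Manual Sections 3.14 and 3.17 lead to Section 6.2, and the pointer in Section 3.3 concerns prohibited, cautionary and allowed medication, not required prophylaxis. Much of this stands: Section 6.2 probably does govern. But a requirement that ends below a stated minimum still conflicts with it, and Section 5.4 is where a reader would expect to find required concomitant medication.

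A second reply is that the time phrase in Section 6.2 follows the clause on fluid monitoring and might qualify only that. The reading is possible, and the schedules do not say whether prophylaxis means the agent, hydration or both. It still leaves the Day 22 entries in both schedules unexplained. The Section 5.4 lead-in also confines fluids to 15 days, so the mismatch remains whichever component is meant.

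A third reply is that the consequence is small. Precautions concentrate on the early doses ("Tumor lysis syndrome prophylaxis and management for the second dose of ABBV-467 will be managed in the same manner as the first dose"), chemistry is reviewed before dosing, a pre-infusion TLS panel is scheduled at Day 22, higher-risk subjects get additional measures, and if TLS criteria are met "no additional doses should be administered until resolution". This stands and limits the size of the point.

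Finally, the documents do not show whether Day 15 was deliberate. If it was, Section 6.2 and both schedules would have to change instead. That is a fair reservation about the direction of the fix, but the sponsor must still state one rule.

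**Conclusion.** The concern holds. Section 5.4 states a shorter period for a mandatory safety medication than the protocol's own minimum and than both visit schedules. It affects one scheduled infusion per subject, the Day 22 dose, and the Section 5.4 limit falls 7 days short of it. The added TLS risk is not quantified and is probably modest. No DLT definition or count, sample size, endpoint or error rate changes.

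The conclusion assumes that the Section 6.2 period applies to the agent as well as to fluid monitoring, and that the unrestricted schedule entries mean what they say. If the first assumption fails, the conflict with the two schedules remains. The text should be corrected because, followed literally, it drops required prophylaxis at a full-dose infusion for which Table 8 schedules only a pre-infusion TLS panel.

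**What to change.** Reword the Section 5.4 lead-in and its first bullet so that all subjects must receive a uric acid reducing agent (allopurinol or another suitable agent) and hydration as tolerated, before and throughout Cycle 1 including the Day 22 dose, with a reference to Section 6.2. Remove both Day 15 limits. With this change Section 6.2, Appendix D and the Operations Manual can stay as they are. If the sponsor did intend to stop at Day 15, Section 6.2 and both schedules should be changed to say so.

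The cost is two lines of text. Subjects who would have stopped at Day 15 take the agent for 7 more days to reach the Day 22 dose, or 13 more if it continues to Day 28. No statistical quantity changes.

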## 5.5 Withdrawal of Subjects from Treatment and Discontinuation of Study

---

### Discontinuation of Individual Subjects from Treatment

A subject may voluntarily withdraw or be withdrawn from study drug at any time for reasons including, but not limited to, the following:

- Clinically significant abnormal laboratory results or AEs, which rule out continuation of the study drug, as determined by the investigator or the AbbVie Therapeutic Area Medical Director (TA MD).
- An AE that results in a study drug hold of > 28 days.

- Subject experiences progressive disease per IMWG criteria (MM) or IWG and ELN criteria (AML).
- The investigator believes it is in the best interest of the subject.
- The subject requests withdrawal from study drug treatment.
- Eligibility criteria violation was noted after the subject started study drug and continuation of the study drug would place the subject at risk.
- Introduction of prohibited medications or dosages and continuation of the study drug would place the subject at risk.
- The subject becomes pregnant while on study drug.
- Subject is significantly noncompliant with study procedures, which would put the subject at risk for continued participation in the trial.
- Subject is lost to follow-up.
- Study is terminated by the sponsor.

To minimize missing data for efficacy and safety assessments, any subject who discontinues study drug treatment should return for the Final Visit, the 30-Day Safety Follow-Up Visit, and continue to be followed for progression (if discontinued for reasons other than progression) and survival-related endpoints, unless s/he has withdrawn informed consent. Subjects should be advised on the continued scientific importance of their data even if they discontinue treatment with study drug early.

### Discontinuation of Individual Subjects from Study

A subject may voluntarily withdraw or be withdrawn from the study at any time for reasons including, but not limited to, the following:

- The subject requests withdrawal from the study.
- Lost to follow-up.
- Study terminated by the sponsor.
- Death.

Final Visit procedures as described in [Appendix D](#) should be performed when a subject discontinues from the study.

For subjects to be considered lost to follow-up, reasonable attempts must be made to obtain information on the subject's final status. At a minimum, 2 telephone calls must be made, and 1 certified letter must be sent and documented in the subject's source documentation.

AbbVie may terminate this study prematurely, either in its entirety or at any site for reasonable cause provided that written notice is submitted in advance of the intended termination. The investigator may also stop the study at his/her site if he/she has safety concerns. If AbbVie terminates the study for safety reasons, AbbVie will promptly notify the investigator.

## 5.6 Follow-Up for Subject Withdrawal from Study Treatment or from Study

---

For any subject who withdraws informed consent, the procedures outlined for the Final Visit should be completed at the subject's last visit. In addition, if subject is willing, a 30-day follow-up phone call after the last dose of study drug may be completed to ensure all treatment-emergent AE/serious adverse events (SAEs) have been resolved to a  $\leq$  Grade 1 or baseline level or, in the opinion of the investigator, the event is unlikely to resolve.

All attempts must be made to determine the date of the last study drug dose and the primary reason for discontinuation of study drug or study participation. The information will be recorded on the appropriate eCRF page. However, these procedures should not interfere with the initiation of any new treatments or therapeutic modalities that the investigator feels are necessary to treat the subject's condition. Following discontinuation of study drug, the subject will be treated in accordance with the investigator's clinical judgment, irrespective of whether or not the subject decides to continue participation in the study.

In the event a subject withdraws consent from the clinical study, biomarker research will continue unless the subject explicitly requests analysis to be stopped. When AbbVie is informed that the subject has withdrawn and no longer wishes biomarker research to continue, samples will not be analyzed, no new biomarker analysis data will be collected for the withdrawn subject or added to the existing data or database(s). A subject may withdraw consent for optional biomarker research at any time and remain in the clinical study. Data generated from clinical study and/or optional biomarker research before subject withdrawal of consent, will remain part of the study results.

